## Abstract

**Background:**

Cardiac rehabilitation (CR) is an essential component of contemporary management for patients with coronary heart disease, including following an acute coronary syndrome (ACS). CR typically involves education and support to assist people following an ACS to make lifestyle changes and prevent subsequent events. Despite its benefits, uptake and participation in tradition CR programs is low. The use of mobile technologies (mHealth) offers the potential to improve reach, access, and delivery of CR support. We aim to determine the effectiveness and cost-effectiveness of a text-messaging intervention (Text4Heart II) to improve adherence to medication and lifestyle change in addition to usual care in people following an ACS. A second aim is to use the RE-AIM framework to inform the potential implementation of Text4Heart II within health services in New Zealand.

**Methods:**

Text4Heart II is a two-arm, parallel, superiority randomized controlled trial conducted in two large metropolitan hospitals in Auckland, New Zealand. Three hundred and thirty participants will be randomized to either a 24-week theory- and evidence-based personalized text message program to support self-management in addition to usual CR, or usual CR alone (control). Outcomes are assessed at 6 and 12 months. The primary outcome is the proportion of participants adhering to medication at 6 months as measured by dispensed records. Secondary outcomes include medication adherence at 12 months, the proportion of participants adhering to self-reported healthy behaviors (physical activity, fruit and vegetable consumption, moderating alcohol intake and smoking status) measured using a composite health behavior score, self-reported medication adherence, cardiovascular risk factors (lipids, blood pressure), readmissions and related hospital events at 6 and 12 months. A cost-effectiveness analysis will also be conducted. Using the RE-AIM framework, we will determine uptake and sustainability of the intervention.

**Discussion:**

The Text4Heart II trial will determine the effectiveness of a text-messaging intervention to improve adherence to medication and lifestyle behaviors at both 6 and 12 months. Using the RE-AIM framework this trial will provide much needed data and insight into the potential implementation of Text4Heart II. This trial addresses many limitations/criticisms of previous mHealth trials; it builds on our Text4Heart pilot trial, it is adequately powered, has sufficient duration to elicit behavior change, and the follow-up assessments (6 and 12 months) are long enough to determine the sustained effect of the intervention.

**Trial registration:**

Australian New Zealand Clinical Trials Registry, ID: ACTRN12616000422426. Registered retrospectively on 1 April 2016.

**Electronic supplementary material:**

The online version of this article (10.1186/s13063-018-2468-z) contains supplementary material, which is available to authorized users.

## Background

Cardiovascular diseases (CVD) are the leading causes of premature death and disability worldwide, accounting for 30% of all global deaths [1]. By 2030, almost 23.6 million people will die from CVD, mainly coronary heart disease (CHD), and the total number of disability-adjusted life years attributable to CVD is expected to reach approximately 204 million [1]. People with CVD are more likely to develop future cardiac events such as unstable angina, myocardial infarction (MI), and sudden cardiac death [2]. This places a huge burden on healthcare systems, with the US spending US$444 billion on CVD-related treatments in 2010 [3].

Improved diagnosis, treatment, and management have substantially reduced the mortality rate of individuals living with CHD [4, 5]; however, those who have experienced an MI have a 20–40% risk of a recurrent event or death in the next 5 years [4, 5]. Approximately 80% of CHD is caused by modifiable risk factors including physical inactivity, smoking, unhealthy diet, and harmful alcohol consumption [6], and effective evidence-based secondary prevention treatments—such as implementing lifestyle changes and adhering to prescribed medication regimens (self-management)—can aid recovery and reduce recurrent cardiac events. Improvements in lipids, systolic blood pressure, smoking prevalence, and physical activity account for an estimated 47% of the total improvement in case fatality [5].

### Management of CHD

Acute coronary syndrome (ACS) encompasses unstable angina, and MI. Following diagnosis of an ACS, patients should receive a range of evidence-based preventive treatments that include appropriate clinical follow-up, as well as referral to programs that provide education and support self-management for the secondary prevention of disease—commonly known as cardiac rehabilitation (CR). A core focus of CR is to encourage people to make healthy lifestyle changes to reduce subsequent cardiac events. Lifestyle behavior changes include regular physical activity, eating a healthy diet, stopping smoking, reducing harmful alcohol intake, and taking medications as per a prescribed regimen [7]. Empowering self-management is critical for people with an ACS to maximize treatment benefits [8].

CR is an essential part of contemporary management for people with an ACS. It has been shown to reduce cardiovascular deaths and hospital readmissions by 25% [7], and is cost-effective for those who participate [9]. A Cochrane systematic review [10] of CR reported a statistically significant reduction in cardiovascular mortality of 26% (odds ratio (OR) 0.74, 95% CI 0.57 to 0.96) and a reduction in all-cause mortality of 13% (OR 0.87, 95% confidence interval (CI) 0.71 to 1.05). This magnitude of effect is consistent with a review of cohort studies and randomized controlled trials (RCTs) [11].

Despite these benefits, CR participation is inadequate in all countries in which it has been assessed [12]. Low levels of patient participation and completion (14–43% after MI) have been reported in Australia, France, the United Kingdom, and New Zealand with high levels of dropout after enrollment [13–17]. Lack of completion reduces the benefits of CR, such as improvements in CVD risk factors [18]. Patient-oriented, medical, and healthcare system factors associated with suboptimal participation include availability, affordability and accessibility of a program, as well as work/domestic commitments and psychological barriers [19, 20]. Current CR delivery approaches do not suit all people and new models are needed to improve the uptake and completion of CR. A range of options should be available for people according to their preferences and needs [21].

### New approaches to enhance self-management

A recent systematic review of alternative models of care found multifactorial individualized telehealth and community- or home-based CR were effective alternatives as they have produced similar reductions in CVD risk factors compared with hospital-based programs [22]. This echoes findings from other reviews of home-based CR [23] and telehealth [24]. There is a paucity of research describing the effectiveness of alternative models of CR in rural, remote, and culturally diverse populations. However, evidence suggests that hospital-based strategies may not be able to deliver effective CR to these populations. Local healthcare systems may need to integrate alternative models of CR, such as brief interventions tailored to individual’s risk factor profiles, as well as community- or home-based programs, to ensure that choices are available that best fit patient’s needs, risk factor profile, and preferences.

### The potential of mobile phone delivered self-management

While telehealth [24] and Internet-based programs have been shown to be effective, they are limited due to predominant reliance on desktop and landline communication, whereas technology is now more mobile. Mobile phones are the most common device for communication worldwide—including developing countries—and are used to deliver behavioral-change programs and improve disease self-management [25]. Mobile phones have potential to influence behavior at a population level because the technology is widely available globally, inexpensive, and allows instant delivery of information [26].

Text-messaging—or short message service (SMS)—is the most widely used mobile phone intervention. Two systematic reviews [27, 28] support the effectiveness of SMS interventions across a range of risk behaviors (e.g., smoking) and chronic conditions (e.g., diabetes and asthma). A 24-week text-messaging intervention in the HEART trial increased walking and leisure time exercise in people who were post ACS (*n* = 171), but did not increase maximal exercise capacity [29, 30]. The TEXT ME trial—which is the largest trial in people with CVD (*n* = 710) [31]—reported statistically significant positive effects on low-density lipoprotein (LDL) cholesterol, and sizeable effects on secondary outcomes such as blood pressure and physical activity. This intervention involved delivery of regular semi-personalized text messages providing advice, motivation, and information that aimed to improve diet, increase physical activity, and encourage smoking cessation. While this study represents a good initial evaluation of a text messaging intervention for enhancing CHD outcomes, future work is still required. First, it was conducted in a single center in Australia with many participants excluded due to language barriers or not owning a mobile phone, which limits its generalizability. Second, the intervention was evaluated as a stand-alone strategy, thus it was unclear whether the intervention was more or less beneficial to those in traditional programs. Third, implementation of the intervention in a real-world setting was not assessed in the study.

We previously conducted the Text4Heart randomized controlled pilot trial (*n* = 123) [32, 33], of a 6-month theory-based program of daily text messages and a supporting website in addition to usual CR services. Using a composite measure of lifestyle change (exercise, diet, smoking, alcohol), we observed a significant treatment effect on adherence to lifestyle behaviors at 3 months (adjusted OR = 2.55, 95% CI 1.12 to 5.84; *p* = .03), but not at 6 months (adjusted OR = 1.93, 95% CI 0.83 to 4.53; *p* = .13). At 6 months, the intervention group had greater self-reported medication adherence (mean difference in scores: 0.58, 95% CI 0.19 to 0.97; *p* = .004), with 51% reporting high adherence compared to 32% in the control condition. Text4Heart was also associated with lowered LDL cholesterol at 6 months compared with control (mean difference: − 0.25, 95% CI -0.49 to 0.003; *p* = .05). Participants reported high fidelity to the text-message component of the intervention, with 85% of intervention participants reading all their messages. Text4Heart was well-received with 84% of participants reporting that the program helped them recover, and 90% of participants would have recommended it to others who had a cardiac event [33]. A definitive trial of Text4Heart to determine its effectiveness using an objective measure is now required to determine the sustained effect of the intervention for augmenting existing cardiovascular services.

### Aims

To determine the effectiveness and cost-effectiveness of the Text4Heart II self-management program—in addition to usual care—to improve adherence to medication and lifestyle change in people with an ACS. A second aim is to use the RE-AIM framework [34] to inform the potential implementation of the Text4Heart II program to augment existing CR services with two district health boards in Auckland, New Zealand.

### Hypotheses

Text4Heart II will improve self-management of ACS, as seen by increased adherence to medication and lifestyle behaviors at 6 and 12 months compared to standard CR care alone,Text4Heart II will be cost-effective, andText4Heart II will be imminently scalable for roll out within the existing healthcare system in New Zealand (district health boards)

## Methods

The Text4Heart II trial is a two-arm, parallel, superiority RCT conducted in two large metropolitan hospitals in Auckland, New Zealand. The study protocol is in accord with the Standard Protocol Items: Recommendations for Interventional Trials (SPIRIT) 2013 Statement [35], and was prospectively registered in the Australian New Zealand Clinical Trials Registry on 1 April 2016, (ACTRN12616000422426). The intervention is described according to the Consolidated Standards of Reporting Trials (CONSORT)-eHealth Checklist [36]. The trial schedule is presented in Fig. 1, and the SPIRIT Checklist is reported in Additional file 1.

**Fig. 1 Fig1:**
[figure not shown]
Schedule of enrollment, interventions, and assessments (Standard Protocol Items: Recommendations for Interventional Trials (SPIRIT) Figure)

### Study population and recruitment

Adults who are clinically stable, able to read English, and provide informed consent are invited to participate into the study either while inpatients, or shortly after discharge following ACS or post percutaneous coronary intervention. Exclusion criteria include untreated ventricular tachycardia, severe heart failure, life-threatening co-existing disease with life expectancy below 1 year, and significant exercise limitations other than CVD. Potential participants will be given information sheets by a researcher and informed consent will be obtained either in writing, or verbally if the participant is already discharged.

All patients admitted with ACS or who undergo angiography are registered in the All New Zealand Acute Coronary Syndrome Quality Improvement register (ANZACS-QI) [37]. ANZACS-QI collects detailed information on risk factors, diagnosis, investigations, as well as management and complications during admission, and is embedded in > 90% of hospitals in New Zealand. Data are able to be linked to laboratory results and dispensing from chemists. Anonymized linkage to patients’ unique National Health Index number allows data to be obtained on mortality and rehospitalization for subsequent analysis [38]. This study design, utilizing the strengths of the clinical registry combined with the specific clinical trial protocol, provides a unique opportunity to collect study data at low cost and with no additional participant burden.

### Sample size

A total of 330 participants (165 per group) will provide 80% power at the 5% level of significance (two-sided) to detect an absolute difference of 15% between the two groups, in the proportions of participants adherent to medication 6 months after randomization (assuming a control rate of 30%). This is a conservative control rate and is based on our self-reported Text4Heart pilot data, and New Zealand research that found only 60% of patients had a Medication Dispensing Ratio (SDR) > 0.8 for statins only [39]. This value is likely to be lower when all classes of medication (statins, antihypertensive, and antiplatelet therapies) are considered. If the control rate was indeed 60% then a total of 304 participants would be required to detect an absolute difference of 15%; thus, we would be adequately powered with our proposed sample size.

### Intervention and control

All participants will receive usual care, which includes CR support. In addition, those allocated to the Text4Heart II intervention arm will receive a personalized, automated program of CR delivered via text message over 24 weeks. The overall goals of the intervention are to encourage and promote adherence to medication, healthy diet, stress management, regular exercise, reduced alcohol consumption, and smoking cessation (if applicable). Participants will be able choose additional focussed intervention modules at baseline that address risk factors that they identify as most relevant to them, such as physical activity, heart healthy diet, stress management, and smoking cessation.

Participants receive one message per day for the first 12 weeks, a technical support phone call at 12 weeks, and five messages per week for the remaining 12 weeks. Messages will be personalized (including participants’ names) and sent at times to suit participants. The intervention is predominantly unidirectional but participants will be able to reply to text messages and a researcher will answer within 24 h. All participants will be offered brief training at enrollment on how to read, delete, and save text messages. Messages are categorized into four groups (see below). Non-smokers receive one to two general heart health messages, one to two physical activity messages, and one to two dietary messages per week. Smokers receive one general heart health message, one to two physical activity messages, one to two dietary messages, and one to two smoking-cessation support messages per week.

At registration, intervention group participants will select their preferred receipt times for educational (early morning, late morning, early afternoon, late afternoon, or evening) and medication reminder messages to ensure that the timing is appropriate for their needs. Details of the text-message content are provided below.

### Intervention content

#### General heart health and medication adherence

General health information messages that include facts about risk factors and medication will be provided. Messages will include information and strategies to help participants adhere to their prescribed medication regimen—including information on the value of taking medication to reduce recurrent events and hospitalization, reminders to have a regular check-up with their physician, enhancing self-management, and addressing illness perceptions and medications beliefs. In addition, advice will be given about contacting their physician if unwell, practical tips on how to improve lifestyle though habit formation and environmental prompts, and how to enlist support from others.

#### Physical activity

Participants will receive messages derived from the successful HEART trial [29, 30], that address the importance of being physically active. Message content will include suggested activities, key strategies to enhance uptake and maintenance of physical activity (e.g., goal setting, self-monitoring), and a generic exercise prescription that suggests the type, frequency, duration, and intensity of exercise.

#### Dietary behavior

Participants will be supported to reduce dietary saturated fat and salt intake, and to manage their weight. All content was developed, pre-tested and successfully piloted prior to the Text4Heart II trial [40]. Participants will receive text messages promoting healthy eating strategies, advice on choosing healthy food, and food preparation. The messages focus on supporting behavior-change strategies.

#### Smoking cessation

Participants who smoke tobacco will receive components of the successful STOMP text-messaging smoking-cessation intervention [41–43]. They will be sent regular messages providing smoking-cessation advice and support (e.g., symptoms to expect on quitting, tips to avoid weight gain and to cope with craving, advice on avoiding smoking triggers).

All messages are grounded in established psychological (Common Sense Model) [44] and behavior-change (Social Cognitive) theory [45] and will focus on modifying perceptions of the symptoms, timeline, causes, consequences, understanding of, personal control over, and ability of treatment to prevent, CVD [46], as well as altering the key mediators of behavior change including self-efficacy, social support, and motivation.

### Outcomes

All outcomes are assessed at 6 and 12 months post randomization. The primary outcome is the proportion of participants adhering to medication at 6 months. Medication adherence is defined as SDRs of 80% for statins, antihypertensive, and antiplatelet therapy classes of medication (calculated separately)—consistent with guideline-recommended therapy [47]—where SDR is calculated as the number of days that the supply is obtained divided by the number of days in the observation period. Participants’ community pharmacy dispensing records will be linked using their unique National Health Index number via the National Pharmaceuticals Collection database. This approach has been used successfully in New Zealand to assess statin use [39]. To adjust for days not covered due to death or days spent in hospital these periods are subtracted from the 6-month coverage time. The number of days supplied will be estimated from strength per unit and daily dose variables summed from pharmacy claims during the observation period. To account for any previous supply of the medication (before discharge), medication claims in the 3 months prior to admission are collected. The SDR for each class of medication (statins, antihypertensive, and antiplatelet therapies) will be recorded as secondary outcomes.

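### The primary adherence ratio sums supply by claim date and looks back only before admission, so a late fill can overstate coverage and a fill between discharge and randomization can be lost

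*Protocol article*

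**What the plan says.** All of this is in the protocol article, under Outcomes unless noted.

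- **Threshold and level.** "Medication adherence is defined as SDRs of 80% for statins, antihypertensive, and antiplatelet therapy classes of medication (calculated separately").
- **Ratio.** "where SDR is calculated as the number of days that the supply is obtained divided by the number of days in the observation period".
- **Numerator.** "The number of days supplied will be estimated from strength per unit and daily dose variables summed from pharmacy claims during the observation period".
- **Adjustment for death and hospital days.** "these periods are subtracted from the 6-month coverage time". This acts on the denominator; no matching step for the numerator is given.
- **Prior supply.** "To account for any previous supply of the medication (before discharge), medication claims in the 3 months prior to admission are collected".
- **Time origin.** "All outcomes are assessed at 6 and 12 months post randomization".
- **Enrolment** (Study population and recruitment). People are invited "either while inpatients, or shortly after discharge following ACS" or after percutaneous coronary intervention. The same section allows verbal consent from those already discharged, so enrolment after discharge is a planned route.

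The 12-month adherence outcome is to be derived in a similar way (Secondary outcomes), and the class-level ratios are secondary outcomes. All of them inherit the rule.

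**The concern.** Two features of the stated rule do not measure what the 80% cut-off is meant to capture.

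First, a claim enters the numerator by its date and brings its whole supply with it. A supply collected shortly before the window closes therefore counts in full, although most of it covers days after the window.

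Second, the look-back ends at admission while follow-up starts at randomization. For someone randomized after discharge, a fill made between the two dates lies in neither period. If the observation period is instead meant to start at discharge, days before randomization enter the outcome. The text does not say which is intended.

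Both features act on the binary primary endpoint, where moving a person across 80% changes the result. The first can turn low coverage into adherence; the second can do the reverse.

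**Working it through.** **Inputs.** From the article: 80% cut-off; six-month window; N = 330 (165 per group); 30% control rate; 15-point difference; two-sided 5%; alternative control rate 60% with N = 304. Assumed, because the article gives no values: a window of 182 days (days 0 to 181) and supplies of 90 or 30 days. The cut-off is then 0.8 × 182 = 145.6 days.

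**1. The plan's own figure.** Normal approximation with pooled variance under the null:

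power = Φ{[Δ√n − 1.96√(2p̄(1−p̄))] / √(p₁(1−p₁) + p₂(1−p₂))}

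With n = 165, p₁ = 0.30, p₂ = 0.45 and p̄ = 0.375: (1.927 − 1.342)/0.676 = 0.865, so power is 80.6%. The required total is 326 against the stated 330. For 60% versus 75% it is 304, as stated. The sample size reproduces.

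**2. Late fill.** Ratio as written = sum of days supplied by claims in the window / 182. Coverage = days in the window with supply in hand / 182.
- 90-day fills on days 0 and 170: as written, 180/182 = 99%; covered, (90 + 12)/182 = 56%.
- In general, with a first 90-day fill on day 0 and a second on day t (t ≥ 90), covered days are 90 + (182 − t). This is below 145.6 for every t from 127 on, while the written ratio stays at 99%.
- 30-day fills on days 0, 40, 80, 120 and 175: as written, 150/182 = 82%; covered, (120 + 7)/182 = 70%.

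**3. Death during the window.** A single 90-day fill on day 50 and death on day 100: as written, 90/100 = 90%; covered, 50/100 = 50%. The denominator is shortened and the numerator is not.

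**4. Lost fill.** Randomization seven days after a 90-day fill, then fills on days 88 and 183. Only the day-88 claim is dated in the window, so the written ratio is 90/182 = 49%. Covered days are 83 (days 0 to 82) plus 90 (days 88 to 177), giving 173/182 = 95%.

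**5. The two errors can cancel.** With the same day −7 fill and on-time refills on days 83 and 173, the written ratio is 180/182 = 99% and coverage is (83 + 90 + 9)/182 = 100%. The lost fill is offset by the untruncated last one. Harm depends on refill timing.

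**6. Consequence for power.** Suppose a share f of truly non-adherent people is counted adherent in both arms and no one is misclassified the other way. Each rate p becomes p + f(1 − p), and the difference becomes Δ(1 − f). At f = 10%, the rates are 0.30 + 0.10 × 0.70 = 0.37 and 0.45 + 0.10 × 0.55 = 0.505, a difference of 13.5 points. Power at N = 330 for assumed f:

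| f | 30% vs 45% | 60% vs 75% |
|---|---|---|
| 0 | 80.6% | 83.2% |
| 5% | 75% | 80% |
| 10% | 70% | 77% |
| 20% | 59% | 70% |

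**7. How often.** A one-class simulation with exponential refill gaps (mean 3 to 40 days), first fill on day 0, put the share of all people wrongly counted adherent anywhere from about 0% to 37%, depending on the assumed gap and supply length. Nothing in the article narrows this range.

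**The case against.** The strongest reply is that this reads a fixed rule into a condensed article. Truncation, overlap and stockpiling rules are programming detail that a full protocol or analysis plan may hold. The ratio's definition can be read as a count of days. Collecting earlier claims implies some carry-over accounting, and the mention of discharge suggests coverage may start there, in which case no discharge fill is lost. The method has been used before in New Zealand for statins, and the linkage is blind to allocation. Finally, the 15 points in the Sample size section concern the measured outcome, and its 60% figure is itself an SDR result, so the plan states no 15-point difference in true coverage to be diluted.

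Much of this limits the point without removing it. The more specific sentence on the numerator says the days are summed over claims. The look-back, the time origin and enrolment after discharge are all stated, and they do not fit together; starting at discharge would solve the lost fill only by admitting days before randomization. Earlier use for statins does not settle how the window works in a trial timed from randomization.

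Three stronger readings are not supported:
- **Two drugs in one class are double counted.** The ratio is reported per class, but the text does not say whether claims are summed by product or across products. One 90-day fill of each of two drugs would score 180/182 = 99% with 90/182 = 49% covered if they were summed. That is a risk to rule out, not a stated rule.
- **The measured adherence rate will be too high.** The two errors run in opposite directions and can cancel, so the net shift is unknown.
- **The planned difference will shrink by a particular amount.** Any such number comes from an assumed refill pattern.

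**Conclusion.** The point holds in limited form. As written, the primary-outcome ratio can misclassify people at the 80% cut-off: upwards through supply that runs past the window end or death, and downwards through fills made after discharge but before randomization. The worked cases (99% scored with 56% covered; 49% scored with 95% covered) rest on an assumed 182-day window and 90-day supplies. They show what the literal rule permits, not how common it is. The second error concerns only people randomized after discharge, whose number is not given.

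If misclassification is unrelated to arm, the main harm is a diluted difference and lost power, not a false positive. The fall from 80.6% to about 70% assumes 10% of non-adherent people are counted adherent in both arms, and treats 30% and 45% as true-coverage rates. This is a worthwhile correction to the primary-endpoint definition before analysis; it does not show that the endpoint is invalid or that the trial is underpowered.

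**What to change.** Define the ratio as the proportion of days covered, computed from a day-by-day supply array:

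1. State day 0 explicitly and tie it to randomization.
2. Carry in unused supply from all fills from three months before admission through randomization, so that the interval after discharge is included.
3. Truncate supply at the last day of the window or at death.
4. Count each day at most once.
5. Treat hospital days the same way in numerator and denominator.
6. State how co-prescribed drugs in one class are combined.
7. Keep the summed ratio as a sensitivity analysis.

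Apply the same definition to the 12-month and class-level outcomes, and fix it before unblinding. It uses the same linked dispensing claims, extended to cover the interval up to randomization. The cost is wording and some extra programming. The downside is less direct comparability with the earlier New Zealand statin study, which the sensitivity analysis largely preserves.
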